### Secondary outcome measures

The PU risk factors will be measured at baseline, 3, 6 and 12 months. Questionnaires will be sent out at baseline, 3, 6 and 12 months.

#### PU risk factors

Prior to the measurement, the participant will be asked not to eat for ≥ 6 h, smoke or consume tobacco ≥ 6 h, consume alcohol or food/drinks that contain caffeine or are rich in polyphenols ≥ 12 h and to avoid exercise ≥ 24 h [43].

#### Local circulation

The participant will be transferred from the wheelchair to a bed and placed in a supine position. After a 20-min resting period [36] the local circulation will be determined by measuring the Blood Flow with Color Doppler in the profunda femoris artery (deep femoral artery). The artery will first be measured in Brightness mode (b-mode) transversal for localization just proximal to the femoral bifurcation. Then the probe will be rotated till longitudinal and slide distally just after the femoral bifurcation where the profunda femoris artery lays most superficial for data collection. The Lumify L12-4 (Philips, USA) is a 12-4 MHz linear array transducer which will be attached to a Samsung Galaxy tab S7+ (Model SM-T970). Color Doppler will be obtained using the Fast Flow function of the software and with the lowest possible insonation angle (always < 60°) [43]. Data analysis will be done with a custom-designed script in Matlab which is made in collaboration with Philips and will include custom edge-detection, wall tracking and colour flow analysis.

#### Muscle thickness

Muscle thickness of the hamstrings (biceps femoris) and the gluteal muscles will also be measured using the Philips Lumify L12-4 ultrasound system.

The muscle thickness of the gluteal muscles will be measured separately due to the different anatomical position origin and insertion wise. So there is made a separate scanning protocol to capture the gluteus maximus and one which captures the medius and minimus in one picture. For both measurements, the participant will lay in a lateral position. Both measurements will start with palpating the trochanter major as a landmark. From there the probe will be placed longitudinally towards the most superficial part of the trochanter major, so with the caudal side of the probe (the side towards the trochanter) rotated 10–15° more posterior. From there, the probe slides a couple of centimetres more cranially so the fossa of the ilium will be visible [44].
For the gluteus maximus, the probe will be moved more posterior to the thickest part of the gluteus maximus. This is located on the inner upper quadrant of more medial from the posterior superior iliac spina and the piriformis line [45]. There the probe will be rotated 35–45° till perpendicular to the muscle in the longitudinal axis.For the gluteus medius and minimus, the probe will be moved more cranial and medial towards the groin area. There the fossa of the ilium will be used as a bony landmark which is visible as a small dent.

The biceps femoris (long head) will be measured with the participant lying in a partial prone/side position. The measurement will be performed in B-mode and starts from the origin of the hamstring (ischial tuberosity) with the probe transversal. From there the probe will be rotated, till in the longitudinal axis and slide downwards and slightly laterally to follow the biceps femoris long head [44].

In both cases, a 3-s clip will be made, while making a fan shape movement to visualize the thickest part of the muscle. When the thickest part is visible, 1 picture will be made in B-mode and saved for later offline analysis using Image J. The whole process repeats till 3 pictures are collected. The first step of the analysis will be to draw lines on the muscle contours to highlight the superficial and deep aponeurosis. Step two is drawing straight lines between both aponeuroses; one in the middle of the muscle and either one or two lines relatively more to the right and left (how much depends on the visibility of the muscle). The distance between the lines between both aponeuroses determines the muscle thickness at different parts of the muscle. The average muscle thickness will be calculated by adding the measured distances and dividing them by the number of lines drawn [46–48].

#### Interface pressure distribution

Interface pressure distribution will be measured using a Boditrak PRO2 (Vista Medical), a 46.5 × 46.5 cm soft flexible mat with 1024 sensors (32×32), each measuring a maximum of 260 mmHg at a 60-Hz frequency. Each participant will be measured while sitting still in his/her own wheelchair with an adaptation time of 5 min followed by a 5-min measurement. Using custom Matlab routines, the mean ischial tuberosities pressure and the pressure gradient (indicative of shear force) will be calculated. The prominent pressure points visible in the measurement, with the highest pressure value are defined as the ischial tuberosities (left and right IT). A selection of the 3 × 3 sensors surrounding the highest values will be used to calculate the mean IT pressure. The pressure gradient will be calculated by subtracting the average of the 16 surrounding sensor values from the IT pressure.

#### Self-reported outcome measures

##### Mobility and activity limitation

*Mobility and activity limitation* will be measured with the Dutch Physical Activities Scale for Individuals with Physical Disabilities (PASIPD) [49, 50].

##### Health-related quality of life

*Health-related quality of life* will be measured with the World Health Organization Quality of Life-5 questionnaire (WHO-QoL-5) [51]. For the economic evaluation, health-related quality of life will also be expressed in terms of Quality Adjusted Life Years (QALYs). For this purpose, the EQ-5D-5L will be administered. The participants’ EQ-5D-5L health states will be converted into utility scores ranging from 0 (“death”) to 1 (“optimal health”) using the Dutch tariff, and QALYs will be estimated using linear interpolation between measurement points.

##### Participation

*Participation* will be measured with two scales; the Utrecht Scale for Evaluation of Rehabilitation- Participation (USER-participation) [52] and the 68-item Sickness Impact profile (SIP-68) [53]. Both scales will be used because the SIP-68 measures influence of illness and/or health complaints on daily functioning while the USER-participation also measures objective data like how many hours spent in a certain activity.

##### Anxiety and depression

*Anxiety and depression* will be evaluated with the Hospital Anxiety and Depression Scale (HADS) [54].

##### Sleep quality

*Sleep quality* will be evaluated with the Pittsburgh Sleep Quality Index (PSQI) [55].

##### Fatigue

*Fatigue* will be evaluated with the Fatigue Severity Scale (FSS) [56].

##### Self-care capacity

*Self-care capacity* will be evaluated with a combined questionnaire and exist of questions in the field of health and SCI. First part includes 18 of the 22 performance-related questions of Bloemen-Vrencken et al. which will have 4 answering options which are scored as follows: never (0), sometimes (1), often (2) and always (3). Total score ranges from 0 (never performing any health behaviour) up to 54 (always performing all health behaviours) [57].

The second part consists of 15 knowledge-related questions earlier used in a Dutch study but not yet described in literature. The questions have 5 answering options and are scored as follows: certainly not true (0), not true (1), no opinion (2), true (3) and certainly true (4). Total score ranges from 0 (no knowledge related to SCI) and 60 (has all the knowledge and information about SCI). A total health behaviour score will be calculated by summing up the scores of each item.

##### Cost data

Costs will be assessed from a societal and a healthcare perspective. From the societal perspective, intervention, other healthcare, unpaid productivity, informal care, presenteeism and absenteeism costs will be included, whereas only costs accruing to the formal Dutch health sector will be included for the healthcare perspective. Resource use data will be collected using cost questionnaires administrated at baseline 3, 6, 9 and 12 months. Intervention costs will be micro-costed. The use of other healthcare services (i.e. primary healthcare, secondary healthcare, medication) will be valued using Dutch standard costs and prices derived from an online pricelist of pharmaceutical products (www.medicijnkosten.nl). Informal care (i.e. care by family and friends) and unpaid productivity losses (i.e. productivity losses related to the fact that participants might not be able to perform unpaid activities, such as volunteer work) will be valued using a recommended Dutch shadow price. Presenteeism and absenteeism will be assessed using a modified version of the IMTA Productivity Cost Questionnaire (iPCQ). Presenteeism and absenteeism will be valued using gender-specific price weights and the friction cost approach will be used for valuing absenteeism [58].

##### Process evaluation

Parallel to the RCT, a mixed methods process evaluation will be conducted using the RE-AIM model [59]. The aims of the process evaluation are (1) to evaluate recruitment, reach and implementation of the daily ES, and participants’, care takers’ and key stakeholders’ experiences of taking part in daily ES to explain program outcomes, including unintended outcomes; (2) to evaluate the views of rehabilitation specialist on the usage of ES as a rehabilitation method; (3) to investigate facilitators and barriers for the adoption, implementation and maintenance of daily ES of gluteal and hamstring muscles combined with usual care; (4) to explore dose-response association between the degree of adherence and effectiveness; (5) to provide recommendations for improvement of the intervention beyond the research setting. The mixed-method design of this process evaluation will include interviews with; the participant, caregivers and specialist. Focus groups with a rehabilitation specialist, researchers, nurse practitioners coordinators and managers, field notes and a question included in the ES questionnaire and diary [60, 61]. Interviews will be held at T1 and after T3, focus group at T3, while questionnaire and diary data will be collected throughout the trial. For further details, see Appendix 1.

### Participant timeline {13}

Figure 1 shows the study design flow chart with the participant timeline.

**Fig. 1 Fig1:**
[figure not shown]
Study design flow chart

### Sample size {14}

The sample size for this study is based on the anticipated difference in the selected primary outcome, i.e. PU incidence. To detect a clinically relevant difference in incidence of PUs of 25% (35% vs. 10%) with alpha = 0.05 and power = 90%, 45 participants in each group are needed. Taking into account a dropout rate of 10%, we need to recruit a total of 100 participants (i.e. 50 participants per group).

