### Trial design {8}

A prospective multicentre RCT will be conducted with an economic and process evaluation alongside. One hundred participants with a chronic SCI will be randomly assigned to either an intervention or control group. It is a superiority trial that aims to evaluate whether daily ES (intervention group) is more effective than usual care (control group) on the prevention of pressure ulcers.

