## Assignment of interventions: allocation

### Implementation {16c}

#### Sequence generation {16a}

Randomization will be done by the research assistant of Reade. Participants will be randomly assigned to either the intervention or control group in a 1:1 ratio with a web-based randomization program (studyrandomizer.com). A permuted block algorithm will be used with a variable block size with a minimum of 4, a maximum of 8 and an increment of 2. Randomization will be stratified for rehabilitation centre and for two age groups; i.e. 18–70 years and ≥70 years. Randomization list will only be available to the local researcher of the rehabilitation centre, the executive investigator and principal investigator. The research assistant of Reade is also the one who completes the Case Report Form (CRF) and keeps everyone posted on how many participants are enrolled to the study.

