#### Effect analysis

An intention-to-treat analysis will be performed using a logistic mixed model with having had a PU during 12-month follow-up (yes/no) as a dependent variable and as independent variables the study group variable (intervention or usual care group) and any potential confounding variables. Two levels will be identified; i.e. rehabilitation centre and patient. The necessity of using a random intercept and/or a random slope will be assessed using the -2 log likelihood test. If both turn out not to be necessary, a regular logistic regression analysis will be performed. Also, as maximum likelihood estimation cannot be used to deal with missing data in these analyses, missing data will be multiple imputed using Multivariate Imputation by Chained Equations (MICE) and pooled estimates will be calculated using Rubin’s rules [57].

An intention-to-treat analysis will also be performed for the secondary outcomes using a linear mixed model for continuous outcomes (e.g. quality of life). Three levels will be identified: i.e. rehabilitation centre, patient and time. Within these models, the secondary outcomes will serve as the dependent variable, a study group variable (intervention or usual care group), interaction terms for study group and time and all confounding variables will be the independent variables. Again, the necessity of using a random intercept and/or a random slope will be assessed using the -2 log likelihood test.

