#### Economic evaluation

Cost-effectiveness analyses will be performed according to the intention-to-treat principle. Missing data will be imputed using Multivariate Imputation by Chained Equations (MICE) and pooled estimates will be calculated using Rubin’s rules [57]. Cost and effect differences will be estimated using linear mixed models or seemingly unrelated regression (SUR) analyses, depending on the number of required random intercepts and/or slopes [58]. Incremental cost-effectiveness ratios (ICERs) will be calculated by dividing the difference in costs by those in effects. BCa bootstrapping with 5000 replications will be used to estimate the uncertainty surrounding the ICERs and 95% confidence intervals around cost differences. Uncertainty will be shown by plotting cost-effectiveness planes and cost-effectiveness acceptability curves [59]. Sensitivity analyses will be performed to assess the robustness of the results (e.g. per-protocol analysis, complete-case analysis, human capital approach).

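### 45 per group does not give 90% power at two-sided 5% (it gives about 82%); the figure is reached only with a one-sided 5% test that the protocol never declares

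*Protocol article*

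**What the plan says.** The Sample size section bases the trial's size on the primary outcome, pressure ulcer incidence. The target is a "difference in incidence of PUs of 25% (35% vs. 10"%), and the section continues "with alpha = 0.05 and power = 90%, 45 participants in each group are needed". It then allows for loss to follow-up: "Taking into account a dropout rate of 10%, we need to recruit a total of 100 participants (i.e. 50 participants per group").

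Allocation is equal, as the Sequence generation section confirms: "Participants will be randomly assigned to either the intervention or control group in a 1:1 ratio". The Effect analysis section makes the primary endpoint binary per participant, using a "logistic mixed model with having had a PU during 12-month follow-up (yes/no) as a dependent variable".

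The article does not say whether alpha is one- or two-sided. The Trial design section has a directional aim ("It is a superiority trial that aims to evaluate whether daily ES (intervention group) is more effective than usual care (control group") but declares no one-sided test. The Effect analysis section gives neither a significance level nor an interval level for the primary comparison. The only interval level in the article concerns the economic evaluation: "95% confidence intervals around cost differences".

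**The concern.** An unqualified alpha of 0.05 in a superiority trial is normally read as two-sided. On that reading, 45 per group is well below what 35% versus 10% needs for 90% power, so the printed result disagrees with its printed inputs.

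This calculation is the only justification for the trial's size. If the test is two-sided, the planned type II error is nearer 18% than 10%, and anyone weighing a non-significant result would credit the trial with more sensitivity than it had. If the test is one-sided at 5%, the chance of a false claim of benefit is twice that of a two-sided 5% test (5% against 2.5% in that direction). The Discussion says a positive result could lead to wide implementation, so readers should be told which standard applies.

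**Working it through.** **Inputs.** From Sample size: p1 = 0.35, p2 = 0.10, alpha = 0.05, power = 0.90, dropout 10%. From Sequence generation: 1:1 allocation. Derived: difference 0.25, squared 0.0625; mean proportion 0.225; pooled term 2 × 0.225 × 0.775 = 0.34875 (square root 0.5906); unpooled term 0.35 × 0.65 + 0.10 × 0.90 = 0.3175 (square root 0.5635). Normal quantiles: 1.960 (two-sided 5%), 1.645 (one-sided 5%), 1.2816 (90% power).

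**Formulas for n per group**
- Pooled: n = (z_alpha × 0.5906 + z_power × 0.5635)² / 0.0625
- Unpooled: n = (z_alpha + z_power)² × 0.3175 / 0.0625
- Arcsine: n = 2 (z_alpha + z_power)² / h², with h = 2 arcsin√0.35 − 2 arcsin√0.10 = 0.6226

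**Reproducing 45.** With one-sided 5% and 90% power, the pooled formula gives (1.645 × 0.5906 + 1.2816 × 0.5635)² / 0.0625 = (0.9714 + 0.7221)² / 0.0625 = 45.9. Two-sided 5% gives (1.1575 + 0.7221)² / 0.0625 = 56.5. All three formulas, rounded up:

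| Test, 90% power | Pooled | Unpooled | Arcsine |
|---|---|---|---|
| One-sided 5% | 45.9 → 46 | 43.5 → 44 | 44.2 → 45 |
| Two-sided 5% | 56.5 → 57 | 53.4 → 54 | 54.2 → 55 |

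Other two-sided variants ask for more: 65 with a continuity correction and 66 on the log odds ratio scale. No two-sided variant tried falls below 54. Two-sided 5% with 80% power needs 43 (pooled), 40 (unpooled) or 41 (arcsine), which is near 45 but contradicts the stated 90%.

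**Power of the stated numbers, two-sided 5%.** Pooled: power = Φ[(0.25 × √n − 1.960 × 0.5906) / 0.5635].
- n = 45: (1.6771 − 1.1575) / 0.5635 = 0.922, so power = 82.2%.
- n = 50: (1.7678 − 1.1575) / 0.5635 = 1.083, so power = 86.1%.

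| Two-sided 5% | 45 per group | 50 per group |
|---|---|---|
| Pooled normal | 82.2% | 86.1% |
| Unpooled normal | 84.5% | 88.0% |
| Arcsine | 84.0% | 87.6% |
| Exact, Pearson chi-square | 84.6% | 87.7% |
| Log odds ratio | 76.7% | 80.9% |
| Exact, Fisher | 76.1% | 82.0% |

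No entry reaches 90%, even with no dropout. One-sided 5% with n = 45 gives 89.5% (pooled) and 91.1% (exact chi-square).

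**Detectable difference.** Solving the pooled power formula at n = 45, two-sided 5%, 90% power and p1 = 0.35 gives p2 of about 0.076, a difference of about 27 points.

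**Dropout.** 45 / 0.9 = 50 per group, 100 in total. This step is correct.

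**The case against.** The strongest reply is that the article never says two-sided. At one-sided 5% the figure of 45 does reproduce, and the aims are worded directionally. On that view nothing is miscalculated, and the only fault is a missing word that the full protocol (the article cites version 2.5) may supply. It is fair that the power shortfall depends on the two-sided reading. It is also fair that the 95% interval in the economic evaluation says little about the primary test, so it is not relied on here. Still, directional wording is ordinary superiority language and does not declare a one-sided test. The objection also does not clear the sentence as printed: its numbers either disagree under the usual reading or agree only through an undisclosed choice.

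A second reply is that 82% is one formula's answer, while the planned analysis is a logistic mixed model with possible covariates and imputation. That stands in part. None of these figures models that analysis, and across methods the two-sided power at 45 per group runs from about 76% to 85%, a type II error of 15% to 24%. The method should therefore be named beside any restated figure. Choice of formula does not explain the discrepancy: the gap is 9 to 12 participants per group, against a spread of 3 between the standard formulas.

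A third reply is that a correction costing only words cannot be serious. The correction is indeed cheap, but the figure it corrects is the trial's headline power.

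**Conclusion.** The concern holds. On the conventional two-sided 5% reading, 45 evaluable participants per group give about 82% power for 35% versus 10%, not 90%, and 54 to 57 would be needed by the standard formulas. Retaining all 100 gives about 86%. At 90% power the stated 45 is obtained only with a one-sided 5% test, which the article declares nowhere.

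The percentages assume the protocol's own incidences, equal groups and an unadjusted comparison of two proportions. The type II error of about 18% holds for the two-sided test and the pooled formula. The sentence needs correcting under either reading; the dropout allowance does not.

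**What to change.** Settle the sidedness and state it in both the Sample size and the Effect analysis sections.

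- **If two-sided 5%:** replace the power claim with one that matches the numbers and names the method. For example: with 45 evaluable participants per group and two-sided alpha 0.05, power for 35% versus 10% is about 82% by the pooled normal approximation, and about 86% if all 100 contribute. Equivalently, 90% power holds for 35% versus about 7.6%.
- **If one-sided 5% was intended:** declare it in both sections, so that the primary test is carried out and reported at the level on which the trial was sized.

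Either change is wording only and adds no participants. The two-sided version makes the stated power less favourable. Keeping 90% power at two-sided 5% would instead need 57 evaluable per group by the pooled formula. That is 57 / 0.9 = 63.3, so 64 recruited per group and 128 in total, 28 more than planned.

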## Assignment of interventions: blinding

### Who will be blinded {17a}

The wound care nurse, who will analyse the digital photos of the sacral or ischial tuberosity’s region (primary outcome), will be blinded during the whole trial. The assessors who will measure the PU risk factors (secondary outcome) will be blinded during the physical measurements by asking participants to not reveal the group they are in. The process evaluation will be conducted by the researchers (FvN) and (BW). Due to the qualitative nature of the research methods, both researchers will not be blinded during the study. The local research assistants in the rehabilitation centres will not be blinded because of their direct contact with the participants while providing the equipment and instructions and the need to be available for questions about ES. Except for the PI (TJ), all other researchers (SG, MvT and HvD) will be blinded during the trial and analyses.

### Procedure for unblinding if needed {17b}

Breaking the randomization code will only occur in the event of unexpected serious adverse events associated with the intervention. In that case, this will be noted on the CRF form, including the reason why, by the principal investigator (TJ) and/or executive researcher (BW).

## Data collection and management

### Plans for assessment and collection of outcomes {18a}

Not applicable, this trial does not have biological specimens.

